## **4.2. Discussion of Design**

This study will evaluate the pharmacokinetics of UMEC (62.5µg and 125µg) and VI (25µg) for the first time administered as single and repeat inhaled doses and in combinations of UMEC/VI (62.5µg/25µg) and UMEC/VI (125µg/25µg) in healthy Chinese subjects. DB2113208, a study in healthy Japanese with similar design using the same drug GSK573219 and VI has been recently completed. A somewhat higher systemic exposure (on average a 30% increase ) was observed in the combination arm than the mono therapy arms, however, DB2113950, a similar study in UK, showed no clear difference between of UMEC/VI and the individual UMEC and VI arms. Therefore a pharmacokinetic study of the combination UMEC + VI compared with UMEC and VI administered individually will be conducted in healthy Chinese adult volunteers. The crossover study design will be adopted to reduce the inter-subject variability. The balanced incomplete block design optimally balances a thorough investigation of the 5 treatment regimens and the overall length of study duration for each subject.

## **4.3. Treatment Assignment**

Subjects will be assigned to three-period incomplete cross-over treatment sequence in accordance with the randomization schedule generated by GlaxoSmithKline Biometrics, GlaxoSmithKline R&D, prior to the start of the study, using validated internal software. A replacement schedule will also be set up in place along the randomization schedule in case of a decision made to replace an early withdrew subject.

Prior to the start of the study, 20 subjects will be randomly assigned to one of 20 possible treatment sequences with the aim to achieve 10-12 evaluable subjects for each regimen. A description of each regimen is provided in [Table 1](#). The 20 sequences are based on a balanced incomplete block design. In this design as described below, both treatment and possible pair of treatments occur across periods evenly:

| Sequence | Period 1 | Period 2 | Period 3 |
|----------|----------|----------|----------|
| 1        | A        | E        | D        |
| 2        | B        | A        | E        |
| 3        | C        | B        | A        |
| 4        | D        | C        | B        |
| 5        | E        | D        | C        |
| 6        | A        | B        | C        |
| 7        | B        | C        | D        |
| 8        | C        | D        | E        |
| 9        | D        | E        | A        |
| 10       | E        | A        | B        |
| 11       | A        | D        | B        |
| 12       | B        | E        | C        |
| 13       | C        | A        | D        |
| 14       | D        | B        | E        |
| 15       | E        | C        | A        |
| 16       | A        | C        | E        |
| 17       | B        | D        | A        |
| 18       | C        | E        | B        |
| 19       | D        | A        | C        |
| 20       | E        | B        | D        |

#### 4.4. Investigational Product and Other Study Treatment Dosage/Administration

UMEC/VI Inhalation Powder in the Novel Dry Powder Inhaler contains two blister strips. One strip contains a blend of micronised GSK573719A, lactose monohydrate and magnesium stearate. The second strip contains a blend of micronised GW642444M, lactose monohydrate and magnesium stearate. The Novel Dry Powder Inhaler will deliver, when actuated, the contents of a single blister simultaneously from each of the two blister strips. Each blister strip is a double foil laminate containing 30 blisters per strip.

For individual UMEC treatment, the UMEC blister strip may contain approximately 62.5 or 125µg per blister of GSK573719, as the bromide salt.

For individual VI treatment, the VI blister strip will contain approximately 25µg per blister of GW642444 as the triphenylacetic acid salt. The product is overwrapped, with a dessicant, in a foil laminate.

|                                        |                       | Investigational Product                                                                         |                                                                                               |                                                                                                            |
|----------------------------------------|-----------------------|-------------------------------------------------------------------------------------------------|-----------------------------------------------------------------------------------------------|------------------------------------------------------------------------------------------------------------|
| Product name:                          |                       | UMEC                                                                                            | VI                                                                                            | UMEC and VI                                                                                    |
| Formulation description:               | 1 st strip | GSK573719: micronised drug blended with lactose monohydrate and magnesium stearate  | GW642444 micronised drug blended with lactose monohydrate and magnesium stearate  | GSK573719: micronised drug blended with lactose monohydrate and magnesium stearate             |
|                                        | 2 nd strip | N/A                                                                                             | N/A                                                                                           | GW642444: micronised drug blended with lactose monohydrate and magnesium stearate              |
| Dosage form:                           |                       | Novel Dry Powder Inhaler                                                                        | Novel Dry Powder Inhale                                                                       | Novel Dry Powder Inhale                                                                                    |
| Unit dose strength(s)/Dosage level(s): |                       | GSK573719 62.5µg or 125µg per blister                                                           | GW642444 25µg per blister                                                                     | GSK573719 62.5µg or 125µg per blister, GW642444 25µg per blister                                           |
| Route/ Administration/ Duration:       |                       | Inhaled, once daily single dose for 10 days                                                     | Inhaled, once daily single dose for 10 days                                                   | Inhaled, once daily single dose for 10 days                                                                |
| Dosing instructions:                   |                       | 62.5µg or 125µg once-daily for 10 days                                                          | 25µg once-daily for 10 days                                                                   | GSK573719 / GW642444 62.5µg/25µg or 125µg/25µg once-daily for 10 days                                      |
| Physical description:                  |                       | Dry off white powder                                                                            | Dry off white powder                                                                          | Dry off white powder                                                                                       |
| Device:                                |                       | Novel Dry Powder Inhaler 30 doses per unit                                                      | Novel Dry Powder Inhaler 30 doses per unit                                                    | GSK573719:Novel Dry Powder Inhaler 30 doses per unit; GW642444: Novel Dry Powder Inhaler 30 doses per unit |
| Manufacturer/ source of procurement:   |                       | GSK                                                                                             | GSK                                                                                           | GSK                                                                                                        |

N/A=Not Applicable

1. Magnesium stearate 0.6% w/w of total drug product
2. Magnesium stearate 1 % w/w of total drug product
3. The combination product (GSK573719 and GW642444) will be administered to the subject by using novel dry powder inhaler devices(NDPI)

#### 4.5. Stopping Criteria

A subject will be withdrawn from the study if they meet any of the stopping criteria in this section.

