### 1.3. Summary of Risk Management

- The study is being run at a clinical pharmacology contract research organization approved by SFDA, which has relevant emergency services required officially, and has access to the hospital emergency room and the hospital intensive care unit.
- Subjects will be under medical supervision for each investigational product administration while vital signs are assessed. Subjects will remain under medical supervision if the Investigator has found any abnormal safety data.
- Subjects will be monitored during the post dose period for known effects of muscarinic antagonists and in particular tachycardia and arrhythmia. Acceptable limits for changes in these parameters have been established and safety criteria for consideration of subject withdrawal are included in the protocol, see Section 4.5.
- Subjects will be monitored during the post dose period for known effects of  $\beta_2$  agonists and in particular tachycardia. Acceptable limits for changes in these parameters have been established and safety criteria for consideration of subject withdrawal are included in the protocol, see Section 4.5.

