#### **4.5.1. Liver Chemistry Stopping Criteria**

Liver chemistry threshold stopping criteria have been designed to assure subject safety and to evaluate liver event etiology during administration of investigational product and the follow-up period. Investigational product will be stopped if the following liver chemistry stopping criterion is met:

- ALT  $\geq 3 \times \text{ULN}$

**Refer to Section 13, Liver Chemistry Follow-up Procedures, for details of the required assessments if a subject meets the above criteria.**

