#### **4.5.2. QTcF Withdrawal Criteria**

A subject that meets the criteria below will be withdrawn from the study. The QT correction formula used to determine discontinuation should be the same one used throughout the study.

- QTcF > 500 msec (machine or manual overread)

Withdrawal decisions are to be based on an average QTcF value of triplicate ECGs. If an ECG demonstrates a prolonged QT interval, obtain 2 more ECGs over a brief period, and then use the averaged QTcF values of the 3 ECGs to determine whether the subject should be discontinued from the study.

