#### **4.5.3. Other Dose Adjustment/Stopping Safety Criteria**

A subject will be withdrawn from the study if they meet the following stopping criteria:

- Subjects experience intolerable adverse events related to study drug.
- Subjects demonstrate clinically significant and relevant ECG changes.
- Subjects demonstrate clinically significant and relevant changes in laboratory parameters
- Subjects experience resting pulse increases of 40 bpm above the baseline resting heart rate or to a maximum of 130bpm at 2 successive measurements, a minimum of 5 minutes apart and if in the investigator's opinion, following a review of the subject's safety data and discussion with the GSK medical monitor, there are safety concerns.

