## **10.3. Subject Withdrawal Procedures**

### **10.3.1. Subject Withdrawal from Study**

For subjects withdrawn from the investigational product, follow-up procedures should be performed. Relevant pages of the CRF should be completed by the investigator

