### **13. LIVER CHEMISTRY FOLLOW-UP PROCEDURES**

**Refer to the diagram in [Appendix 1](#) for a visual presentation of the procedures listed below.**

The procedures listed below are to be followed if a subject meets the liver chemistry stopping criteria defined in Section [4.5.1](#):

- Immediately and permanently withdraw the subject from study treatment
- Notify the GSK medical monitor within 24 hours of learning of the abnormality to confirm the subject's study treatment cessation and follow-up.
- Complete the "Safety Follow-Up Procedures" listed below.
- Complete the liver event case report forms. If the event also meets the criteria of an SAE (see Section [12.2](#)), the SAE data collection tool will be completed separately with the relevant details.
- Upon completion of the safety follow-up permanently withdraw the subject from the study and do not rechallenge with study treatment.

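### The half-lowest-AUC imputation in 6.3.2.2.2 is not limited to non-quantifiable data, so a profile cut short would be given an artificially low exposure

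*Protocol*

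**What the plan says.** **Imputation.** Protocol 6.3.2.2.2 derives the exposure parameters. If AUC0-∞ (single dose) or AUC0-τ (repeat dose) cannot be obtained, it falls back to AUC0-t', with t' taken across all subjects and treatments within the analyte. It then says that AUC parameters which cannot be calculated are set to half the lowest calculable AUC for that analyte, over all subjects and treatments. No cause is named. Section 6.3.2.2.4, on accumulation, does name the cause of its own fallback: non-quantifiable (NQ) data in the terminal phase.

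**Analysis set.** The PK population in 6.3.2.1 is every treated subject with at least one PK sample obtained and analysed. A short profile therefore stays in.

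**How a profile can be cut short.** Section 4.5 opens: "A subject will be withdrawn from the study if they meet any of the stopping criteria in this section". The QTcF rule in 4.5.2 says "A subject that meets the criteria below will be withdrawn from the study", and 4.5.3 says "A subject will be withdrawn from the study if they meet the following stopping criteria". For the liver criterion, 4.5.1 says "Investigational product will be stopped if the following liver chemistry stopping criterion is met". Section 13 then starts with "Immediately and permanently withdraw the subject from study treatment" and ends with "Upon completion of the safety follow-up permanently withdraw the subject from the study and do not rechallenge with study treatment".

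**After withdrawal.** Section 10.3.1 says "For subjects withdrawn from the investigational product, follow-up procedures should be performed", without listing the procedures. Section 1.3 adds "Subjects will remain under medical supervision if the Investigator has found any abnormal safety data".

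**The concern.** Half the lowest AUC is a reasonable stand-in when exposure was too low to measure. When samples are absent because the subject left or a draw was missed, their absence carries no information that exposure was low. In a subject withdrawn for a QTcF or pulse reaction, exposure may even have been high. The rule as worded would still assign the lowest value in the data set.

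The combination/monotherapy ratios of AUC and Cmax are the primary comparisons in section 6.1. A falsely low AUC on regimen A or B moves the ratio away from showing raised exposure. On C, D or E it moves the ratio towards it. Section 1.1.4 reports that an earlier study found VI AUC 39% higher on concurrent dosing, so raised exposure is the question the study is asked to inform.

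The stopping rules are a secondary matter. All of them end in withdrawal from the study, and none says whether the PK, ECG and vital-sign profile in progress is finished first. If it is not, AUC over the full interval and the 0-4 h weighted-mean QTcF (section 3.2) could be lost.

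**Working it through.** **1. Subjects per regimen.** Counting over the 20 sequences in 4.3: 20 × 3 / 5 = 12 subjects per regimen, with each pair of regimens in 6 subjects. This agrees with the stated aim of 10-12 evaluable subjects.

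**2. What a truncated profile leaves.** Tables 3 and 4 schedule 9 PK, 6 ECG and 7 vital-sign points on Day 1, and 12, 9 and 10 on Days 10-12. The table shows the points outstanding if nothing is taken after the trigger time. These are upper bounds.

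| Trigger | Day 1: PK / ECG / vital signs | Days 10-12: PK / ECG / vital signs |
|---|---|---|
| 15 min | 6/9, 4/6, 4/7 | 9/12, 7/9, 7/10 |
| 1.5 h | 4/9, 2/6, 2/7 | 7/12, 5/9, 5/10 |
| 4 h | 2/9, 1/6, 1/7 | 5/12, 4/9, 4/10 |

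After a 1.5 h trigger, (4 − 1.5)/4 = 62.5% of the 0-4 h QTcF window has no closing ECG. After a trigger at 4 h or later, that endpoint is whole.

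**3. Size of the imputation error.** Let m be the lowest calculable AUC and x the subject's true AUC. The imputed value is m/2. If x ≥ m, then m/2 ≤ x/2, so the AUC is at least halved. When one of n values is divided by f, the geometric mean falls by 1 − (1/f)^(1/n).

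| f | n = 12 | n = 10 |
|---|---|---|
| 2 (smallest case, x = m) | 5.6% | 6.7% |
| 4 (x = 2m) | 10.9% | 12.9% |

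The second row can matter for UMEC. The lowest AUC is taken across treatments, so a 125 µg profile may be given half of a 62.5 µg value. Assuming dose-proportional exposure, a subject at 125 µg whose AUC would have been m at 62.5 µg has x = 2m. Section 1.2.2 reports somewhat more than proportional increase.

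**4. Effect on the treatment ratio.** Assumed model: ln(AUC) with treatment and period fixed and subject random, fitted by generalised least squares to the 48 UMEC profiles (A-D) or the 36 VI profiles (A, B, E). The protocol leaves the model to an SOP and the RAP. If an observation on the combination regimen has weight w in its contrast, halving it lowers the ratio by 1 − 0.5^w. The mean weight is 1/12 = 0.0833, so the average shift is 1 − 0.5^0.0833 = 5.6%. Halving a monotherapy value instead raises the ratio by 2^(1/12) − 1 = 5.9% on average. For single combination-regimen subjects, over within-subject correlation 0 to 1:

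| Ratio | Weight | Downward shift |
|---|---|---|
| A/C, B/D | 0.0536-0.1071 | 3.6-7.2% |
| A/E | 0-0.143 | 0-9.4% |
| B/E | 0-0.125 | 0-8.3% |

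**5. Does the AUC0-t' fallback prevent this?** Take a 1.5 h trigger with no later draws: the last PK sample is at 1 h. If t' must be common to everyone, it becomes 1 h for all subjects on that analyte. If t' stays later, that subject's AUC0-t' cannot be calculated and the imputation applies. Neither result is wanted.

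**The case against.** **The imputation may never be reached.** AUC0-t is still obtained from a truncated profile with enough quantifiable samples, and section 6.3.2.2.6 allows a fallback measure in the treatment comparison. This stands for AUC0-t. For AUC0-t' it exchanges the false low value for a shortened interval in every subject (step 5).

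**The analysis plan may settle it.** Model detail is left to the RAP, so carrying imputed values into the comparison is an assumption. The imputation rule itself, however, is stated in the protocol and carries no limit.

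**Truncation should be rare.** Entry requires QTcF below 450 msec, and withdrawal needs a triplicate mean above 500 msec. The pulse rule needs two successive readings and a discussion with the medical monitor. Section 5.1 allows replacement if a group falls below 10 evaluable subjects. All of this stands and limits the expected impact. Replacement, though, does not remove the truncated subject from the PK population.

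**A stronger reading of the stopping rules.** A reader might infer that non-liver triggers force immediate exit, unlike the liver trigger. The documents do not support this. The opening sentence of 4.5 covers every criterion, liver included, and Section 13 also ends in study withdrawal. The liver procedures ask for liver tests and one PK sample, not for the profile to be completed. Only the staging differs. Nothing forbids completing a profile, and supervision (1.3), follow-up procedures (10.3.1) and AE follow-up (12.6) make some monitoring likely. What remains on this side is an ambiguity.

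**Conclusion.** The imputation rule in 6.3.2.2.2 is too broad and should be narrowed. Read literally, it turns an AUC that is missing for lack of samples into the lowest value in the data set, in a subject whom the PK population retains. One such value, if only halved, costs 5.6% of a 12-subject geometric mean and moves the treatment ratio by a similar amount, in a direction set by the regimen.

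The ratio shift rests on three conditions: a profile is cut short so that its AUC cannot be calculated, the rule is applied as written, and the imputed value enters the comparison under the assumed model. The trigger rate cannot be derived from the document and should be low, and Cmax, AUC0-t and maximum QTcF would usually survive. This is a change to consider, with a small expected effect. The silence on finishing the current profile is a minor companion point.

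**What to change.** **Section 6.3.2.2.2.** Limit the half-lowest-AUC imputation to AUCs that cannot be calculated because concentrations are NQ. Treat AUCs from truncated or absent profiles as missing. State that a truncated profile does not determine t'.

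**Sections 4.5 and 10.3.1 (companion).** State that meeting a criterion stops dosing permanently. The subject, if willing and if the investigator considers it safe, completes the PK, ECG and vital-sign points already scheduled for the profile in progress (to 8 h on Day 1, to 48 h after the Day 10 dose) and the 7-10 day follow-up visit, and is then withdrawn. Criteria and thresholds stay as they are.

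**Cost.** A sentence or two in the PK section and short wording in two others. No new procedure is added. The remaining points are already scheduled in a subject due to be resident to Day 12, and later periods are still spared.

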#### **4.5.1. Liver Chemistry Stopping Criteria**

Liver chemistry threshold stopping criteria have been designed to assure subject safety and to evaluate liver event etiology during administration of investigational product and the follow-up period. Investigational product will be stopped if the following liver chemistry stopping criterion is met:

- ALT  $\geq 3 \times \text{ULN}$

**Refer to Section 13, Liver Chemistry Follow-up Procedures, for details of the required assessments if a subject meets the above criteria.**

#### **4.5.2. QTcF Withdrawal Criteria**

A subject that meets the criteria below will be withdrawn from the study. The QT correction formula used to determine discontinuation should be the same one used throughout the study.

- QTcF > 500 msec (machine or manual overread)

Withdrawal decisions are to be based on an average QTcF value of triplicate ECGs. If an ECG demonstrates a prolonged QT interval, obtain 2 more ECGs over a brief period, and then use the averaged QTcF values of the 3 ECGs to determine whether the subject should be discontinued from the study.

#### **4.5.3. Other Dose Adjustment/Stopping Safety Criteria**

A subject will be withdrawn from the study if they meet the following stopping criteria:

- Subjects experience intolerable adverse events related to study drug.
- Subjects demonstrate clinically significant and relevant ECG changes.
- Subjects demonstrate clinically significant and relevant changes in laboratory parameters
- Subjects experience resting pulse increases of 40 bpm above the baseline resting heart rate or to a maximum of 130bpm at 2 successive measurements, a minimum of 5 minutes apart and if in the investigator's opinion, following a review of the subject's safety data and discussion with the GSK medical monitor, there are safety concerns.

